### Study design

Because both quantitative and qualitative data will be collected, this study has a sequential explanatory design. This is a superiority trial, with equal allocation to the intervention and control groups. Specifically, qualitative data will be collected after the quantitative phase is finished, and qualitative data with rich contexts will be used to illuminate the quantitative findings. The current quantitative study is a randomized controlled trial with four study arms: (1) a MBTCC group, (2) a MBI group, (3) a TCC group, and (4) a SHE control group. The outcome measures will be collected at four time points: at baseline (T1), after the 8-week intervention (T2), 6 months after the intervention (T3), and 1 year after the intervention (T4). In addition, qualitative evaluation through focus group interviews will be conducted at the end of the 12-month assessment period (T4). The study flowchart is displayed in Fig. 2.

**Fig. 2 Fig2:**
[figure not shown]
Flow chart of the study. MBTCC, mindfulness-based Tai Chi Chuan; MBI, mindfulness-based intervention; TCC, Tai Chi Chuan; SHE, sleep hygiene education

### Participants

Participants will be recruited from community-based elderly centres in Hong Kong. Specifically, three major elderly centres as managed under three non-government organizations (i.e. Yang Memorial Methodist Social Service, Evangelical Lutheran Church Social Service, and Hong Kong Sheng Kung Hui Welfare Council) will be approached. These three centres are in Kowloon, New Territories, and Hong Kong Island, respectively. Social workers from corresponding centres will be approached with an introduction to the research project. They will help recruit suitable participants in their respective centres. Initial screenings will be performed by the social workers according to our inclusion and exclusion criteria. The inclusion criteria are as follows: (1) aged 60 years or above, (2) classified as experiencing sleep disturbances (indication of poor sleep quality through a score > 5 in the Pittsburgh Sleep Quality Index [19]), (3) primary education level or above and able to communicate in Cantonese, (4) able to give informed consent, and (5) no previous experience with meditation or other mind-body techniques (e.g. tai chi or yoga). Elderly people with comorbid diagnoses of schizophrenia, schizoaffective disorder, substance misuse, organic brain syndrome, or intellectual disabilities will be excluded. Eligible participants will be further interviewed by the principal investigators or a research assistant in order to further explain to them the research project, to seek informed consent, and to complete the baseline assessments. After the initial baseline assessment, participants will be randomly assigned to one of the study arms using a list of computer-generated random numbers. The generation of random numbers and their assignment will be performed by a statistician who is unaware of the study aims. Another research assistant, who will assist with the outcome assessment and data analysis, will be kept unaware of the group allocation results. In order to promote participant retention and complete follow-up, the participants will be given cash coupons to thank them after completing the corresponding assessment at each time point. Besides, monthly telephone follow-ups will be conducted by a research assistant to remind the participants to do the home practice.

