### Interventions

#### The MBTCC group

MBTCC will integrate components from both the MBI and TCC groups, as illustrated in the following. The entire intervention consists of eight weekly sessions of 2.5 to 3 h each. Details are shown in Table 2.

**Table 2 Tab2:** Overview of different interventions

Session	MBI	TCC	MBTCC	SHE
1	● Awareness and automatic pilot ● Mindful eating ● Body and breath meditation	● Learning standing pose ● First posture: beginning Tai Chi ● Second posture: gasp sparrow’s tail	● Approaching mindfulness and TCC ● Mindful standing ● Awareness of breathing ● Practice of the first two postures of TCC	● General introduction of sleep disturbances and sleep hygiene ● Diaphragmatic breathing
2	● Keeping the body in mind ● Body scan ● Sitting meditation	● Standing pose ● First two postures ● Third posture: single whip	● Combining the mind and body together ● Mindful sitting ● Practice of the first three postures of TCC	● Understanding of sleep ● Practice of diaphragmatic breathing
3	● Gathering the scattered mind ● Mindful stretching ● Mindful walking	● Learning twisting pose ● Standing pose ● First three postures ● Fourth posture: lift hand upward	● Joining mindfulness and TCC ● Mindful twisting ● Practice of the first four postures of TCC	● Promoting habits and sleep environment ● Systematic muscular relaxation
4	● Expanding awareness ● Sounds and thoughts meditation ● 3-min breathing space	● Twisting pose ● Standing pose ● First four postures ● Fifth posture: white crane spreads wings	● Awareness expansion ● Mindful walking ● Practice of the first five postures of TCC	● Strengthening bed and bedroom as sleep stimulus ● Practice of systematic muscular relaxation
5	● Allowing/letting be ● Meditation in exploring difficulty ● Breathing space meditation	● Learning walking pose ● Standing pose ● First five postures ● Sixth posture: step forward, deflect, parry, punch	● Living with difficulties ● Learning about accuracy in TCC ● Practice of the first six postures of TCC	● Restricting time in bed ● Imagery rehearsal training
6	● Befriending meditation ● Loving-kindness and compassion ● Cultivating friendship towards oneself	● Walking pose ● Twisting pose ● First six postures ● Seventh posture: like sealing, as if closing	● Self-compassion ● Learning about “song” in TCC ● Practice of the first seven postures of TCC	● Diet relating to sleep ● Practice of imagery rehearsal training

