#### The MBI group

The MBI group is mainly based on the basic theory and research of the foundational mindfulness-based stress reduction programme [13]. Within this group, participants will cultivate the learning of mindfulness through various kinds of mindfulness activities, such as body scans, sitting meditation, mindful movements, mindful walking, and mindful eating. The intervention consists of eight weekly sessions of two to two-and-a-half hours each. Modifications to the content were carried out, to make it more suitable for elderly people with sleep disturbances. Information sheets about the MBI will be given to the participants. In order to facilitate practice through homework, each participant will be provided with an audio clip, which will be uploaded to their smartphones. All participants will be advised to practise mindfulness meditation at home on a daily basis, using the audio clip, and record it in a logbook.

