#### The TCC group

TCC is mainly based on a nine-form Yang-style form of TCC, which is a brief and modified version of 64-form Yang-style TCC. It can be easily learned and practised without restrictions on time and space. Within the group, participants will be guided through learning the nine sequential forms of TCC movements. In addition, they will learn TCC post-standing, TCC walking, and TCC twisting. The essence of accuracy, “song”, and tranquillity will also be cultivated throughout the sessions. The entire intervention consists of eight weekly sessions of two to two-and-a-half hours each. Information sheets about the principles and skillsets of each form of TCC will be provided to each participant. Video clips will be provided and uploaded to participants’ smartphones to enable home practice. They will be advised to participate in daily home practice and keep a record of their daily practice.

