### Qualitative focus group interviews

One-fourth of the participants will be selected and invited from each intervention group for focus group interviews at T4. The format of the group interviews will be semi-structured, with a collaborative enquiry of the experiences gained from the respective interventions. The practicability of the programme, perceived therapeutic ingredients, and perceptions of the benefits regarding improvements in sleep disturbances from the participants’ perspectives will be explored and identified through the focus group interviews.

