### Ethical considerations

This proposal has been approved by Human Subjects Ethics Sub-committee from the Hong Kong Polytechnic University (Reference number: HSEARS20210331002-01). An information sheet and a written consent form which has been formally approved by the ethics committee will be distributed to participants when they are invited to take part in the research project. Participation in this study will not make excessive discomfort or other injuries. Observation of mental state and any potential of self-harm behaviours will be closely taken throughout the processes of respective interventions or assessments. When necessary, participants would be advised to consult a professional. Individuals may experience some mild discomforts or tiredness during the MBTCC, MBI, or TCC programme. Such discomforts or fatigue, however, should be no greater than what they experience in everyday life. On the other hand, the participants may get direct therapeutic benefits of improving their sleep problems by taking part in respective interventions. Participants are free to decide whether to participate in this study, and they can revoke their consent and withdraw from the study at any time during the study, without any reason. This decision will not affect their medical care, nor will it cause any unpleasant results.

Informed consent will be obtained in accordance with the Declaration of Helsinki. The investigator will prepare the informed consent form which has been approved by the ethical committee. A properly executed, written, informed consent will be obtained from each participant prior to entering the participant into the trial. Information will be given in both oral and written form and participants will be given ample opportunity to inquire about details of the study. A copy of the signed consent form will be given to the participant, and the original will be maintained with the participant’s records. Any information obtained in this study will remain very strictly confidential, will be known to no one, and will be used for research purposes only. Codes, not names, are used on all test instruments to protect confidentiality. Data will be stored in encrypted files on the computer.

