## Discussion

MBIs and TCC are both perceived as mind-body interventions and share the common feature of a focus on breathing, but they may represent distinct approaches with different mechanisms and philosophical orientations. MBIs focus on stress management via changes in cognitive and behavioural responses and may therefore be conducive to treating rumination or psychological dysfunction. TCC, on the other hand, places a greater emphasis on physical health outcomes and the arousal-related physiological dimensions of sleep disturbance. Thus, *combining both MBIs and TCC has the potential to optimize improvements in sleep disturbance*. However, there is a dearth of evidence to guide clinical practice in regard to the best way to integrate these approaches. The current research study seeks to address this knowledge gap by investigating the combined effects of MBIs and TCC in the management of sleep disturbances.

This study has several potential limitations, including the risk of attrition and selection bias. In order to maintain the distinct benefit of randomization as a mechanism to prevent selection bias, an “as-randomized” analysis keeps participants in the group to which they were initially allocated. To avoid attrition bias, outcome data obtained from all participants are included in the data analysis, regardless of protocol adherence. That is, intention-to-treat analysis will be used as the ideal analysis strategy in this study. In addition, the study entails a long follow-up period. To achieve a high follow-up rate, we will ensure good communication between research personnel and participants, accessibility and convenience to nearby elderly community centres, effective communication channels, and appropriate incentives to continue and ensure that the study is of relevance to the participants.

Nevertheless, the present research project should determine the effects of an integrated MBTCC programme on sleep disturbances among Chinese older adults living in the community. The research findings can allow older adults or healthcare professionals to select appropriate practices. This will produce benefits, satisfaction, adherence, and sustainability in early interventions, which are potentially less costly and have fewer side effects. In addition, an evidence-based alternative intervention, as shown in this study, can help alleviate the burgeoning public health burden of sleep disturbances among older adults living in the community.

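### Bodily harms during home practice have no stated active ascertainment, and the monthly calls already planned are described only as practice reminders

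*Protocol article*

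**What the plan says.** All references are to the protocol article.

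- **What is observed, and when (Ethical considerations).** "Observation of mental state and any potential of self-harm behaviours will be closely taken throughout the processes of respective interventions or assessments". The section adds that participants would be advised to consult a professional when necessary.
- **What is expected (same section).** "Individuals may experience some mild discomforts or tiredness during the MBTCC, MBI, or TCC programme".
- **Where the exposure takes place.** For MBI: "All participants will be advised to practise mindfulness meditation at home on a daily basis, using the audio clip, and record it in a logbook". For TCC: "They will be advised to participate in daily home practice and keep a record of their daily practice". The SHE section likewise advises daily use of its guidelines, with a record. MBTCC is built from MBI and TCC components, and no separate home-practice instruction is given for it.
- **Contact between visits (Participants).** "monthly telephone follow-ups will be conducted by a research assistant to remind the participants to do the home practice". No other purpose is given for these calls, and neither their duration nor that of home practice is stated.
- **Measures.** The listed outcomes and mediators are insomnia severity, interoception, actigraphy, SF-12, rumination and hyperarousal. None is a record of harms. The focus groups at T4 cover "The practicability of the programme, perceived therapeutic ingredients, and perceptions of the benefits regarding improvements in sleep disturbances".
- **What relies on harms being known.** Ethical considerations makes adverse events a possible reason to discontinue study treatment and gives the steering committee a patient-safety remit. Data management has a data monitoring committee review accumulating data and protect participants' interests. Both committees meet every 3 months.

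**The concern.** The stated observation and the stated exposure do not match in two respects.

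The first is content. Observation is described for mental state and self-harm, while the harms the article expects are bodily: discomfort and tiredness.

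The second is setting. Observation is tied to interventions or assessments, while most practice is meant to be done at home. The contact that does reach participants at home encourages practice and is not said to ask about its effects.

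Participants are aged 60 or above and, by the inclusion criteria, new to meditation and other mind-body techniques. If someone strains a joint or falls while practising at home, the stated procedures rely on that person mentioning it unprompted. Volunteered reports are usually less complete than answers to a direct question, and they can vary with how much contact a participant has and what that participant thinks is relevant. The discontinuation rule and the committees can act only on what reaches them. Events not asked about at the time are hard to recover later, and arm-level counts built on volunteered reports would be difficult to interpret.

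**Working it through.** The article states no figure on this point, so there is none to reproduce. The check compares the stated contacts with the period of exposure, and then asks what harm counts from this design could show.

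**1. In-person contact.** Inputs: eight weekly sessions (Intervention and assessment fidelity); T2 after 8 weeks, T3 and T4 at 6 and 12 months after the intervention (Measurements). Assumption: one day per assessment.
- Period after baseline: 8 × 7 + 365 = 56 + 365 = 421 days.
- Contact days: 8 sessions + T2, T3, T4 = 11. Share: 11/421 = 2.6%.
- Year after the programme: T3 and T4 only, 2/365 = 0.5%.
- Interval between those contacts: 365/2 = 182.5 days, about 26 weeks.
- Supervised teaching totals 16 to 24 hours per programme, as stated.

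**2. What the calls could cover.** Their duration is not stated, so a range is needed.
- If they run to T4: about 12 calls after T2. Interval 365/12 = 30.4 days, about 4.3 weeks, in place of about 26.
- If they stop with the 8-week programme: about 2 calls in all and none after T2. The interval stays at about 26 weeks, and only questions at T3 and T4 covering the whole preceding period would help.

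The longer reading is plausible, because the sentence on calls directly follows one on retention and complete follow-up. It remains an assumption.

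**3. What the existing measures could pick up.** The Insomnia Severity Index looks back one week, and actigraphy covers one week per time point. SF-12 and the hyperarousal scale, collected at T1 to T4, could show an average worsening in an arm. None identifies an event, its date or its link to practice.

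**4. What counts could show even with complete ascertainment.** Inputs: 64 per arm; 30% attrition (Sample size), so 0.70 × 64 = 44.8, about 45. With zero events in an arm, the one-sided 95% upper limit is 1 − 0.05^(1/n), or roughly 3/n.

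| n per arm | exact limit | 3/n |
|---|---|---|
| 64 | 4.6% | 4.7% |
| 45 | 6.4% | 6.7% |

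Full ascertainment with no events would thus leave rates of up to about 5% to 7% per arm open. That bounds what any side-effect statement could say; it does not show that an event would be missed.

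**The case against.** The strongest reply is that this is a condensed article. Data Availability says a full protocol exists, and adverse-event forms and call scripts commonly sit there. Their absence here is not an error. That stands, and the point therefore rests on what is stated: the scope given for observation and the purpose given for the calls. If the full protocol is wider, these sections describe it too narrowly.

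A second reply is that the word interventions may include home practice, since each single-component programme describes its daily practice or guidelines as part of it. The wording permits this. Even so, the content remains mental state and self-harm, and the only stated links to the home are a practice record and a reminder call.

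Three stronger readings are tempting but not supported.

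- **That harms will go unseen.** A reader might infer this from the reminder-only calls. But adverse events are a named reason to discontinue, which presupposes that some reach the investigator. Data management requires adequate source records for each participant, and two committees meet quarterly. Nothing prevents a participant from raising a problem during a call.
- **That SHE is ascertained differently.** The expected-discomfort sentence omits SHE, although Table 2 gives that arm content such as "Restricting time in bed". That sentence describes expected risk and does not govern data collection. The observation sentence exempts no arm.
- **That the Discussion plans a safety conclusion.** It speaks of early interventions "which are potentially less costly and have fewer side effects". The phrase is hedged, names no comparator and is not a trial hypothesis.

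**Conclusion.** The point holds in a limited form. As stated, bodily harms arising in home practice have no active ascertainment that is the same in all four arms, while the discontinuation rule and the committees' roles depend on such events being known. No sample size, power or efficacy figure changes.

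The size of the gap is about 26 weeks between in-person contacts after T2. It could shrink to between 4 and 5 weeks using calls already planned, on the assumption that those calls run to T4. The conclusion also assumes that the article describes the scope of observation and the purpose of the calls accurately; the full protocol could show otherwise. It does not say that harms will be missed, only that no one is stated to ask about them. The change is worth making because it is cheap now and cannot easily be made good after follow-up.

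**What to change.** - **Participants.** State how long the calls run. Add a short fixed set of questions to each call, worded identically in all four arms: injury or fall, pain or discomfort, tiredness, low mood or self-harm thoughts, and any care sought.
- **Measurements.** Ask the same questions at T2, T3 and T4, covering the whole period since the last contact. Place them after the outcome questionnaires, so that an answer revealing the programme cannot affect a masked assessment.
- **Ethical considerations and Data management.** Reconcile the scope of observation, the expected discomforts and the adverse-event reason for discontinuation with this ascertainment. State that the answers go to the two existing committees.
- **Reporting.** Give counts by arm, and limit any side-effect statement from this trial to those counts and their confidence limits.

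If the full protocol already provides for this, it is enough to bring the article's sections into line with it.

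Cost: a few minutes per call, a short form, one results table and more minor events to log. No new staff, visits or participants are needed. The article does not say whether the caller knows the allocation. If so, probing could differ by arm; the fixed script limits that risk but does not remove it.

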### Sample size

A four-armed randomized controlled pilot trial was recently conducted by the authors. A total of 76 community-dwelling older adults with symptoms of sleep disturbance took part in the pilot trial, with an attrition rate of 30%. They were randomly assigned to four different groups, including a MBI group, a TCC group, a MBTCC group, and a SHE group. The results of this pilot study are summarized in Table 1. Although the pilot study yielded moderate to large effect sizes (between .42 and .78), this variation implies that the effect sizes might be sample-dependent or context-dependent. In the current study, a larger sample size is therefore considered to be more desirable because it could pave the way for the identification of a small and hidden effect. Hence, in this power analysis, the effect size is set to .25 and the alpha level is .05. It is suggested that, to obtain the power level of .86 for the main effect and .97 for the interaction effect, at least 180 total participants are needed. Given that this study is longitudinal in nature and attrition (assuming the rate is 30%) is likely, an additional 76 participants will be recruited, resulting in a total of 256 participants (64 per arm).

**Table 1 Tab1:** Comparison between four study arms in a pilot study

Variable	MBI group (*n* = 22)		TCC group (*n* = 23)		MBTCC group (*n* = 10)		SHE group (*n* = 21)		Effect size (MBI vs SHE), Cohen’s *d*	Effect size (TCC vs SHE), Cohen’s *d*	Effect size (MBTCC vs SHE), Cohen’s *d*	Effect Size (MBI vs TCC), Cohen’s *d*
	Pre, mean (SD)	Post, mean (SD)	Pre, mean (SD)	Post, mean (SD)	Pre, mean (SD)	Post, mean (SD)	Pre, mean (SD)	Post, mean (SD)				
ISI	17.27 (3.69)	15.64 (3.44)	17.22 (3.59)	15.70 (3.21)	17.10 (3.35)	14.40 (3.10)	16.95 (3.28)	16.90 (3.55)	− 0.44	− 0.42	− 0.78	− 0.03
SF12 (Phy)	11.05 (2.75)	11.55 (2.06)	11.48 (2.88)	12.91 (2.91)	11.90 (2.60)	13.90 (2.23)	12.76 (3.39)	12.52 (3.27)	0.24	0.52	0.69	− 0.32
SF12 (Men)	16.18 (3.66)	18.05 (3.75)	16.09 (3.40)	16.96 (3.05)	17.40 (3.20)	19.50 (3.21)	17.67 (3.90)	17.95 (3.50)	0.41	0.16	0.48	0.28
RRQ	3.06 (.79)	2.61 (.77)	2.89 (.88)	2.79 (.78)	3.23 (1.03)	2.68 (.84)	3.13 (.83)	3.10 (.66)	− 0.51	− 0.08	− 0.57	− 0.41
HS	62.23 (6.75)	57.59 (6.29)	61.39 (6.89)	53.52 (6.90)	64.00 (5.94)	54.70 (6.93)	63.29 (5.88)	61.48 (6.77)	− 0.44	− 0.93	− 1.24	0.47

*MBI* mindfulness-based intervention, *TCC* Tai Chi Chuan, *MBTCC* mindfulness-based Tai Chi Chuan, *SHE* sleep hygiene education, *ISI* Insomnia Severity Index, *SF12 (Phy)* Chinese (HK) Short Form 12 – Physical health, *SF12 (Men)* Chinese (HK) Short Form 12 – Mental health, *RRQ* Rumination-Reflection Questionnaire, *HS* hyperarousal scale

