### Hypotheses

Hypothesis 1. Participants in the MBTCC group will report significantly greater improvements at 8-week (T2), 6-month (T3), and 12-month (T4) follow-ups in regard to measures of the primary outcome of insomnia severity, compared with participants in the MBI-alone group, the TCC-alone group, and the SHE control group.Hypothesis 2. Participants in the MBI-alone group will experience significantly greater improvements than those in the SHE control group in the primary outcomes across time, in which the beneficial effects on insomnia severity will be mediated by rumination and psychological function.Hypothesis 3. Participants in the TCC-alone group will experience significantly greater improvements than those in the SHE control group in the primary outcomes across time, in which the promising effects on insomnia severity will be mediated by the arousal level and physical function.Hypothesis 4. The favourable effects of the MBTCC group on insomnia severity will be mediated by all the proposed mediators.

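### The .25 effect size is described as small but works only as Cohen's f, where it is about the pilot effect; the .86 and .97 power are omnibus and do not describe MBTCC versus MBI or TCC

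*Protocol article*

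**What the plan says.** The Sample size section reports a 76-person, four-arm pilot. Its ISI effects of .42 to .78 are labelled Cohen's d in Table 1. The section warns that such effects may depend on sample or context and prefers a larger sample "because it could pave the way for the identification of a small and hidden effect". It then states: "Hence, in this power analysis, the effect size is set to .25 and the alpha level is .05". The result is given as follows: "to obtain the power level of .86 for the main effect and .97 for the interaction effect, at least 180 total participants are needed". Recruitment is set at 256, or 64 per arm.

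Hypothesis 1 is worded by comparator. MBTCC is to show greater improvement in insomnia severity at T2, T3 and T4 "compared with participants in the MBI-alone group, the TCC-alone group, and the SHE control group". Table 1 prints effect sizes for each active arm against SHE and for MBI against TCC. It prints none for MBTCC against MBI or MBTCC against TCC.

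**The concern.** An unlabelled .25 directly after d values of .42 to .78 reads as a cautious planning value, well below the pilot. Power for main and interaction effects in a four-arm repeated design is normally computed on Cohen's f, and f and d are different scales. If .25 is f, the promised caution may not exist.

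The second issue is what the power describes. The trial's distinctive question is whether the integrated programme adds to either component. High power for an omnibus group or interaction term can come largely from differences with SHE. If MBTCC does not separate from MBI or TCC, a reader who sees 86% and 97% may take that as evidence of no added benefit when the design had much less power for those contrasts.

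**Working it through.** **Inputs.** From the Sample size section: effect size .25, alpha .05, N = 180 (45 per arm). From Table 1: ISI means, SDs and group sizes (MBI 22, TCC 23, MBTCC 10, SHE 21). Assumptions: two-sided tests, one follow-up visit, no multiplicity adjustment, and a baseline-to-follow-up correlation rho that the article does not give.

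**1. Which metric is .25?** Between-group power in a repeated-measures ANOVA with m visits uses λ = N f² m / (1 + (m − 1)rho), on 3 and 176 df.
- If .25 is d between the extreme arms, f over four arms is at most .25/2 = .125. The best case is m = 4 and rho = 0: λ = 180 × .015625 × 4 = 11.25, power .80. At rho of .3 to .7 with 2 to 4 visits, power is .29 to .50. The stated .86 is out of reach.
- If .25 is f, m = 4 and rho = .83 give λ = 45/3.49 = 12.9, power .86. So .86 is attainable.

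Hence .25 must be Cohen's f.

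**2. What f = .25 means.** With four arms, the gap between the extreme arms is 2f = 0.50 SD (two arms at each end) to f√8 = 0.71 SD (two arms in the middle).

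**3. The pilot on the same one-way scale.** ISI changes are −1.63 (MBI), −1.52 (TCC), −2.70 (MBTCC) and −0.05 (SHE). Their mean is −1.475 and their SD (divisor 4) is 0.943. The pooled baseline SD is 3.51 and the pooled post SD 3.36.
- Changes: 0.943/3.51 = .27, or 0.943/3.36 = .28. Weighted by group size: .24 and .26.
- Post means: 0.884/3.36 = .26. Weighted: 0.775/3.36 = .23.

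The pilot f is therefore .23 to .28, and .25 lies inside that range.

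**4. The missing component effects.** Table 1's ISI values are reproduced by d = J × (difference in change)/(pooled baseline SD of the two arms), with J = 1 − 3/(4df − 1):
- MBI vs SHE: −1.58/3.496 × 0.982 = −0.44
- TCC vs SHE: −1.47/3.446 × 0.982 = −0.42
- MBTCC vs SHE: −2.65/3.302 × 0.974 = −0.78
- MBI vs TCC: −0.11/3.639 × 0.983 = −0.03

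All four match the printed values. The same formula gives:
- MBTCC vs MBI: −1.07/3.591 × 0.975 = −0.29
- MBTCC vs TCC: −1.18/3.522 × 0.976 = −0.33

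The standard error of the first is about √(1/10 + 1/22 + 0.29²/64) = 0.38, so its 95% interval runs from about −1.0 to +0.5. The second is equally imprecise.

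**5. Power at 45 per arm.** Noncentral t with noncentrality d√(45/2)/√(1 − rho²). The lower figure in each cell uses the d values of step 4. The upper uses the raw differences over the common SD of 3.51 (0.305 and 0.336).

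| rho | MBTCC vs MBI | MBTCC vs TCC |
|---|---|---|
| unadjusted | 27-30% | 34-35% |
| .7 | 48-52% | 58-60% |
| .8 | 62-66% | 73-75% |

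For MBTCC vs SHE at d = 0.78, unadjusted power is about 95%.

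**6. Difference detectable with 80% power at 45 per arm, SD 3.5.** Unadjusted: 0.597 SD, or 2.1 ISI points. Multiplying by √(1 − rho²): 0.52 SD or 1.8 points at rho .5, and 0.43 SD or 1.5 points at rho .7. The pilot differences were 1.07 (vs MBI) and 1.18 (vs TCC) points.

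**The case against.** Several things can fairly be said for the plan.

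- The powered terms match the model in Data processing and analysis, which examines time, group and their interaction. This is true, but Hypothesis 1 is worded as comparisons with each arm, and no figure is given for those.
- One visit without baseline adjustment is the pessimistic end, since a repeated-measures mixed model is planned. This stands, and it is why a range is shown. Taking post means instead (d of 0.37 and 0.41) gives 41% and 49% unadjusted, and 68% and 77% at rho .7. Averaging T2 to T4 with baseline adjustment, under a constant effect and compound symmetry, gives 56% and 67% at rho .5, and 69% and 80% at rho .7, for d of 0.29 and 0.33. Most of these still fall short of the stated .86.
- The component effects rest on 10 MBTCC participants. This also stands, so the detectable difference is the sounder statement.
- Saying that .25 equals the pilot effect depends on the scale. On a repeated-measures scale that averages in baseline, the pilot f is about .12 to .19 (group) and .12 to .14 (interaction). That makes .25 larger than the pilot, so it does not restore the claim of caution.

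A reader might also infer that .86 and .97 are miscalculated. The article does not support that. Four visits with rho about .83 give .86 for the group term, and an alternative effect-size convention with a sphericity factor of .7 gives .968 for the interaction. Those settings are assumed, but they show that the figures cannot be called wrong. Leaving such inputs to the full protocol is normal for an article. Nor does the attrition allowance matter: 256 × 0.70 = 179.2 against 180 is less than one person.

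**Conclusion.** The point holds in two parts. First, .25 must be Cohen's f for the stated .86 to be possible. On the one-way scale it is about the pilot's own ISI effect (.23 to .28), so calling it a provision for a small effect is wrong as written. This part rests only on the article's own figures and standard power formulas.

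Second, .86 and .97 describe omnibus tests and not MBTCC against MBI or TCC. For those contrasts, at pilot-sized effects and one visit, power is roughly 27-35% unadjusted, 48-60% at rho .7 and 62-75% at rho .8. The size of this shortfall depends on an assumed correlation and on imprecise pilot estimates.

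Two stronger conclusions might be drawn and are not supported. One is that Hypothesis 1 succeeds only if all three comparisons are significant together: the article names three comparators but sets no joint criterion. The other is that recruitment must rise: the finding concerns what the sample size is said to deliver.

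**What to change.** Revise the Sample size paragraph as follows:

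- Label .25 as Cohen's f, equivalent to 0.50 to 0.71 SD between the extreme arms and close to the pilot value, and remove the statement that it targets a small effect.
- State that .86 and .97 apply to the omnibus main and interaction tests only.
- Add the detectable ISI difference, or the power, for MBTCC vs MBI and MBTCC vs TCC at 45 per arm over a stated correlation range. At SD 3.5 and 80% power, one visit, this is about 2.1 points unadjusted, 1.8 at rho .5 and 1.5 at rho .7.
- Commit to reporting these two comparisons with confidence intervals, so that a non-significant result is not read as showing no added benefit.

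The cost is text only, with no extra recruitment and no design change. The downside is that the stated power becomes less favourable for the component comparisons.
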